#### Secondary Endpoint

Secondary outcome measures will include a composite clinical endpoint of MACCE at 30 days follow-up, defined as (i) all-cause mortality; (ii) non-fatal myocardial infarction; (iii) transient ischaemic attack or stroke; and (iv) heart failure with or without hospitalization (see Table 1 of Appendix for more details).

### Sample Size Determination

In a recent audit of STEMI patients across several participating sub-Saharan African hospitals, we found an all-cause mortality rate of 14% and an 18% cumulative risk of readmission with post-MI heart failure requiring in-hospital treatment at 30 days. We have based our power calculations on these recent audit data, using a primary combined event rate of 30%. We have estimated the effect size to be a 25% relative risk reduction in the 30-day event rate of all-cause death and heart failure hospitalization. We selected a 25% reduction as this effect size would be clinically meaningful and achievable for such a high-risk population. To demonstrate a 25% reduction in the primary composite endpoint, we will need to recruit 1078 STEMI patients in total to achieve 80% power, at the 5% significance level. Therefore, allowing for a conservative 10% drop-out rate at 30 days, we intend to recruit 1200 STEMI patients across the 20 recruiting centres over the 24-month recruitment period. The sample size does not include participants recruited into the observational arm of the study.

### Statistical Analysis

All efficacy endpoints will be analysed according to the intention-to-treat principle. The primary analysis will be a comparison of all-cause death and post-MI heart failure hospitalization event rates at 30 days after randomization between the RIC and sham control arms in all randomized STEMI participants. Differences in means among the randomized groups will be analysed using the analysis of variance (ANOVA) test and, if required, the Turkey post hoc test, and differences in proportions using the χtest, or Fisher exact test, as appropriate. Follow-up will be measured from date of randomization until date of occurrence of the composite event (death or heart failure for primary analysis, and death, non-fatal MI, transient ischaemic attack or stroke, or HF with or without hospitalization for the secondary analysis) or end of the study. The primary outcomes will also be analysed in prespecified subgroups defined in our statistical analysis plan. Survival curves of study groups will be compared using the Kaplan-Meier method, and significance will be assessed using the Log-rank test. Cox proportional hazards regression models will be fitted to identify factors associated with the hazard of occurrence of the composite event. Strength of association will be expressed as a hazard ratio, with 95% confidence intervals and Wald test *p* value. All tests will be two-sided, and a *p* value < 0.05 will be considered significant. The Stata (TX, USA) statistical software will be used for data analysis.

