### Study Endpoints

#### Primary Endpoint

For the purpose of this trial, all endpoints were consistent with the 2017 cardiovascular and stroke endpoint definitions for clinical trials consensus document [17].

The primary composite endpoints of the study will be all-cause death and early post-MI heart failure. The latter is defined as (a) pre-discharge (in-hospital) heart failure or (b) heart failure hospitalization within 30 days of discharge from index myocardial infarction (see Table 1 of Appendix for more details).

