## Appendix

**Table 1. Tab1:** Definition of study endpoints according to the 2017 cardiovascular and stroke endpoint definitions for clinical trials [17]

Pre-discharge heart failure	I. New or worsening symptoms of heart failure (dyspnoea, decreased exercise tolerance, fatigue, or symptoms of worsened end-organ perfusion or volume overload) II. Objective clinical evidence of heart failure and fluid retention (such as pulmonary crepitations/crackles, raised JVP, S3 gallop, peripheral oedema, increasing abdominal distension/ ascites, or rapid weight gain thought to be related to fluid retention) III. Radiological evidence of pulmonary congestion/ oedema IV. Increased cardiac biomarkers (such as BNP > 500 pg/mL or NT-proBNP > 2,000 pg/mL) V. The initiation of intravenous or the significant augmentation of oral loop diuretic therapy
Heart failure hospitalization at 30 days	I. An admission ≥ 24 h II. A diagnosis of heart failure made by the treating clinician III. The initiation of intravenous or the significant augmentation of oral loop diuretic therapy
Non-fatal myocardial infarction	Acute re-infarction MI that occurs in the first 28 days after the index admission for STEMI, defined by [18]: I. Recurrent ischaemic symptoms II. New ST segment deviation in at least two contiguous leads III. A ≥ 20% increase between an immediate cTn value taken at re-admission and a subsequent cTn value taken 3–6 h later, exceeding the 99th percentile upper range limit
Transient ischaemic attack	A transient episode of focal neurological dysfunction caused by brain, spinal cord or retinal ischemia, without acute infarction
Stroke	An acute episode of focal or global neurological dysfunction caused by brain, spinal cord, or retinal vascular injury as a result of haemorrhage or infarction
Heart failure without hospitalization	An event that meets the clinical criteria for heart failure but does not meet the length-of-hospital stay, i.e. an admission < 24 h

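### The sections on endpoint, sample size and analysis disagree on whether in-hospital heart failure counts in the primary composite, and on its 30-day window

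*Protocol article*

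**What the plan says.** All references are to the protocol article.

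- **Primary Endpoint.** The composite is introduced as "The primary composite endpoints of the study will be all-cause death and early post-MI heart failure". The heart failure part is then defined as "a) pre-discharge (in-hospital) heart failure or (b) heart failure hospitalization within 30 days of discharge from index myocardial infarction".
- **Statistical Analysis, primary-analysis sentence.** "The primary analysis will be a comparison of all-cause death and post-MI heart failure hospitalization event rates at 30 days after randomization". In-hospital heart failure is not named, and time runs from randomization.
- **Statistical Analysis, follow-up sentence.** The composite event is given as "death or heart failure for primary analysis", with no reference to hospitalization.
- **Sample Size Determination.** The audit inputs are 14% all-cause mortality and "an 18% cumulative risk of readmission with post-MI heart failure requiring in-hospital treatment at 30 days". The effect is set as a "25% relative risk reduction in the 30-day event rate of all-cause death and heart failure hospitalization".
- **Appendix, Table 1.** Pre-discharge heart failure has its own row, with symptoms, signs, imaging, biomarkers and diuretic treatment. The next row is a different event: "Heart failure hospitalization at 30 days I. An admission ≥ 24 h", plus a clinician's diagnosis and diuretic treatment.

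**The concern.** The primary endpoint of a confirmatory trial should sort each patient as event or non-event in one way only. Here the sorting depends on which section is followed. A patient who develops heart failure during the index stay, goes home alive and is not readmitted is an event under the Primary Endpoint section. Under the primary-analysis sentence, read with Table 1, the same patient is not.

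Two event rates, two effect estimates and two p-values could therefore be taken from the same data, each traceable to the published text. The sample size has the same problem: if it was built for one composite and the trial is judged on the other, the stated power does not describe the test that will be made.

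**Working it through.** **1. The texts side by side**

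| Section | Pre-discharge heart failure counted? | Window for heart failure |
|---|---|---|
| Primary Endpoint | Yes, component (a) | 30 days from discharge for hospitalization |
| Statistical Analysis, primary-analysis sentence | Not named | 30 days from randomization |
| Statistical Analysis, follow-up sentence | Yes, if heart failure is read without qualification | From randomization |
| Sample Size Determination | Not named; audit input is readmission | 30 days |

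Table 1 gives the two heart failure events separate criteria, so the term for hospitalization does not by definition absorb the in-hospital event. The Secondary Endpoint section also uses hospitalization as a real qualifier, since it counts heart failure with or without it.

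On the window: for a patient discharged *d* days after randomization, the Primary Endpoint section counts a readmission up to day *d* + 30, and the primary-analysis sentence only up to day 30. A readmission between those days is classified differently.

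**2. The plan's own sample size**

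Inputs from Sample Size Determination: sham rate p1 = 0.30; 25% relative reduction, so p2 = 0.75 × 0.30 = 0.225; power 80%; significance level 5%. Statistical Analysis makes tests two-sided. Randomization gives equal allocation.

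n per arm = [1.960·√(2p̄(1−p̄)) + 0.842·√(p1(1−p1) + p2(1−p2))]² / (p1−p2)², with p̄ = 0.2625.

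- 1.960 × √0.3872 = 1.2196
- 0.842 × √0.3844 = 0.5218
- n = (1.7414)² / 0.005625 = 539.1 per arm

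Twice 539 is the stated 1078 (rounding up gives 1080). Dropout: 1078 / 0.9 = 1198, stated as 1200. The arithmetic is sound.

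**3. Which composite the 30% describes**

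The article bases the power calculation on 14% mortality and 18% heart failure readmission. With no overlap these sum to 32%; if independent, 1 − 0.86 × 0.82 = 29.5%. The 30% is thus accounted for by death and readmission alone, with no allowance for patients whose only event is in-hospital heart failure.

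**4. Power for the wider composite**

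The article gives no pre-discharge heart failure rate. **Assumption:** such patients add 10 or 15 points to the sham rate. With 539 per arm, power = Φ{[√539·(p1−p2) − 1.960·√(2p̄(1−p̄))] / √(p1(1−p1)+p2(1−p2))}.

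| Case | p1 | p2 | Argument of Φ | Power |
|---|---|---|---|---|
| As planned | 0.30 | 0.225 | (1.741 − 1.220)/0.620 = 0.841 | 80.0% |
| +10 points, 25% reduction on all events | 0.40 | 0.300 | (2.322 − 1.322)/0.671 = 1.490 | 93.2% |
| +15 points, 25% reduction on all events | 0.45 | 0.3375 | (2.612 − 1.354)/0.686 = 1.832 | 96.7% |
| +10 points, no effect on added events | 0.40 | 0.325 | (1.741 − 1.333)/0.678 = 0.603 | 72.7% |
| +15 points, no effect on added events | 0.45 | 0.375 | (1.741 − 1.365)/0.694 = 0.543 | 70.6% |

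The last two rows keep the 7.5-point difference. With an assumed addition of 5 to 20 points, the same two cases span about 70% to 99%.

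These are bounding cases, and power passes through 80% between them. With 10 points added and a 7% reduction on those events, p2 = 0.225 + 0.10 × 0.93 = 0.318. Power is then Φ{(1.904 − 1.330)/0.676} = Φ(0.849) = 80.2%.

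**The case against.** The best defence is that this is loose wording. The section headed Primary Endpoint lists the components and points to Table 1, so it is the natural controlling text. The Abstract and the follow-up sentence in Statistical Analysis both speak of heart failure without requiring hospitalization. Sample Size Determination calls its target the primary composite endpoint, and planning on the audit data at hand does not redefine an endpoint. The article also refers to a statistical analysis plan, which is not shown and may fix one definition.

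Much of this stands, and it rules out three stronger readings that a reader might draw.

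- *That the analysis deliberately uses hospitalization only.* The article never says so, and its follow-up sentence points the other way. What it shows is inconsistency, not the adoption of a narrower endpoint.
- *That the trial is underpowered.* The range in the calculation rests on an assumed 10 to 15 points with no anchor in the article. Power may rise or fall, and the low end requires no effect at all on every added event.
- *That the primary result will be picked after unblinding.* The text leaves room for that, but does not show that it will happen.

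The defence does not remove the contradiction. The narrower wording sits in the operative sentence for the primary analysis and in the sentence that sets the effect size, and Table 1 keeps the two events apart. An unseen plan may settle the matter, but the published sections would still disagree. Nothing here is a complaint about missing detail.

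**Conclusion.** The point holds as a contradiction in the text of the primary endpoint. It must be resolved before unblinding, on the strength of the wording alone. The sections disagree on whether in-hospital heart failure counts and on where the 30 days start, and the Statistical Analysis section is inconsistent with itself on the first.

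The sample size calculation is correct for death plus heart failure hospitalization. The stated 80% should be read as applying to that composite. For the composite in the Primary Endpoint section, power is indeterminate from the article: about 71% to 97% under the assumed addition of 10 to 15 points, according to whether the 25% reduction carries over to the added events. Neither a loss nor a gain of power is established.

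**What to change.** Before unblinding, state one primary composite and one time window with one origin. Use them in Primary Endpoint, Sample Size Determination and Statistical Analysis. Keep the planned comparison of 30-day event rates; nothing in this point calls for a different form of analysis.

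If the composite in the Primary Endpoint section governs:

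- change the primary-analysis sentence so that it names pre-discharge heart failure;
- report death plus heart failure hospitalization as a secondary analysis;
- in Sample Size Determination, either say that the 30% rate and 80% power refer to the narrower composite, or give a sourced event rate for the wider one and restate the power.

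If the narrower composite governs, remove component (a) from the primary definition and align the follow-up sentence. The sample size text can then stand.

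The cost is wording in the protocol, and in the statistical analysis plan if it carries the same ambiguity. No extra trial data are needed. The exception is a restated power for the wider composite, which needs a pre-discharge heart failure rate that the article does not give.

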## Methods

### Study Design

The RIC-AFRICA study is a sub-Saharan African prospective, multi-centre, randomized, phase 3 double-blinded, sham-controlled clinical trial of 1200 STEMI patients across 20 sites in South Africa, Kenya, Sudan, and Uganda. Patients who are ineligible because they present after 24 h will be concurrently recruited into an independent observational arm of the study if they are within 72 h of MI onset. The study will be conducted in accordance with the Declaration of Helsinki and has received approval from the ethics committee of the University of Cape Town (September 10, 2021/ HREC107.2021). Trial enrolment will begin from December 01, 2021, and extend over a 24-month period. The RIC-AFRICA study protocol has been registered at www.clinicaltrials.gov (identifier: NCT04813159), and the study will be conducted and reported according to the CONSORT statement [15]. An independent data and safety monitoring board has been selected to oversee the trial. All participants will provide informed written consent.

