### Randomization

Consenting participants who present within 24 h of MI onset will be randomized to receive either RIC or sham control. Randomization will be conducted via an automated, secure web-based program built into the data capturing software. Randomization will be stratified according to recruiting site and time of MI-onset, using random permuted blocks. The randomization schedule will be conducted in a manner that ensures that 2 participants in stratum 1 (receives thrombolysis within ± 12 h of MI onset) are recruited for every participant in stratum 2 (outside the thrombolytic window but within 24 h of MI onset) and will ensure equal allocation to both the active and sham control arms. The patient, treating clinician, and study investigators will be blinded to the treatment allocation. Willing participants who present between 24 and 72 h of MI onset will be recruited into the concurrently running independent observational arm of the RIC-AFRICA study.

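### The tests named for the primary composite ignore the factors used to stratify randomization; if those factors are prognostic, this is mildly conservative and forgoes about 1 to 3 points of power

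*Protocol article*

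**What the plan says.** Protocol article, Randomization: "Randomization will be stratified according to recruiting site and time of MI-onset, using random permuted blocks". The same section fixes two participants in stratum 1 (thrombolysed within 12 h) for each one in stratum 2 (outside that window but within 24 h), and says the schedule "will ensure equal allocation to both the active and sham control arms". Study Design describes "1200 STEMI patients across 20 sites in South Africa, Kenya, Sudan, and Uganda".

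Protocol article, Statistical Analysis: the primary analysis compares 30-day event rates between RIC and sham in all randomized patients. Proportions are compared by a chi-square test "or Fisher exact test, as appropriate". For time to event, "Survival curves of study groups will be compared using the Kaplan-Meier method, and significance will be assessed using the Log-rank test". Cox models are described as a way of finding factors associated with the hazard, not as a treatment comparison adjusted for the strata. Tests are two-sided at 0.05. None is said to be stratified or adjusted. The only matter this section refers to the statistical analysis plan is the choice of subgroups.

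Protocol article, Sample Size Determination: the sham event rate is taken as 30%, and "We have estimated the effect size to be a 25% relative risk reduction in the 30-day event rate". From this, "we will need to recruit 1078 STEMI patients in total to achieve 80% power, at the 5% significance level".

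**The concern.** Stratified randomization with permuted blocks makes the arms nearly equal in site and onset stratum. The difference between arms then no longer varies through chance imbalance in those factors. A plain chi-square or log-rank test still counts the variation between strata in its standard error. If the strata differ in risk, that standard error is too large, so the test rejects less than 5% of the time under the null and gives up some power under the alternative.

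The article itself gives reason to expect a difference. Its Discussion lists long ischaemia times and delayed presentation among the features that mark a higher-risk population, and stratum 2 consists of later presenters who are not thrombolysed. Twenty hospitals in four countries may also differ in baseline risk. At stake is a little efficiency that the randomization makes available at no cost.

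**Working it through.** **1. The plan's own figure.** Inputs from Sample Size Determination: 30% versus 22.5% (a 25% relative reduction), 80% power, 5% level; two-sided from Statistical Analysis. Pooled two-proportion formula, with mean risk 0.2625:

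n per arm = [1.960 × √(2 × 0.2625 × 0.7375) + 0.8416 × √(0.30 × 0.70 + 0.225 × 0.775)]² / 0.075²
= (1.2196 + 0.5218)² / 0.005625 = 539.1.

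Twice this is 1078, as stated. Dividing by 0.90 for drop-out gives 1198, consistent with 1200. The stated size is therefore that of a plain, unstratified comparison of two proportions.

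**2. Assumptions needed.** The article gives no event rates by stratum or site. The checks below assume a 2:1 stratum mix, an overall sham rate of 30%, 1:1 balance within strata and 1080 evaluable patients. In the simulations this means 36 and 18 patients per site in the two strata, and 40 cells. Stratum risks and site variation are varied.

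**3. Closed form, onset stratum only.** For sham risks r1 and r2, the between-stratum variance is v = (2/3)(r1 − 0.30)² + (1/3)(r2 − 0.30)². The plain test uses 0.30 × 0.70 = 0.21 where the true value is 0.21 − v, so its true level is 2[1 − Φ(1.960 / √(1 − v/0.21))].

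Example, 25/40%: v = (2/3)(0.0025) + (1/3)(0.01) = 0.005; 1 − v/0.21 = 0.9762; 1.960/0.9880 = 1.984; level 4.7%.

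Power is Φ((0.075 − 1.96 × SE) / √V). V is the true variance from within-stratum binomials. SE is the pooled standard error for the plain test, or its within-stratum counterpart for the stratified test, both with 540 per arm.

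| Sham risk, stratum 1 / 2 | v | True level, plain | Power, plain | Power, stratified |
|---|---|---|---|---|
| 30 / 30% | 0 | 5.0% | 80.1% | 80.1% |
| 27.5 / 35% | 0.00125 | 4.9% | 80.1% | 80.3% |
| 25 / 40% | 0.005 | 4.7% | 80.3% | 80.9% |
| 20 / 50% | 0.02 | 3.9% | 81.1% | 83.2% |

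**4. Simulation with sites added.** Chi-square against Cochran-Mantel-Haenszel (CMH) over site × stratum. SD is the between-site standard deviation on the log-odds scale. Where the sham mean is not held at 30%, site variation raises it to about 31%, which explains the slightly higher power in those rows.

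| Sham risk, site SD | Sham mean | Level, chi-square / CMH | Power, chi-square / CMH |
|---|---|---|---|
| 27.5 / 35%, 0.5 | not held | 4.4% / 5.0% | 82.1% / 83.2% |
| 25 / 40%, 0.5 | not held | 4.2% / 4.9% | 82.2% / 83.5% |
| 25 / 40%, 0.5 | held at 30% | 4.3% / 5.0% | 80.7% / 82.2% |
| 20 / 50%, 0.5 | not held | 3.5% / 4.9% | 82.5% / 85.3% |
| 20 / 50%, 0.8 | held at 30% | 3.2% / 5.0% | 81.8% / 85.3% |

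**5. Log-rank.** Plain against stratified by onset stratum only, without site effects: power 81.3% versus 82.0% at 25/40%, and 81.5% versus 84.8% at 20/50%. The true level of the plain test is 4.9% and 3.7% respectively. The direction is the same and the size similar.

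**The case against.** The strongest objection is that the lack of stratification is inferred from silence. The section never calls its tests unstratified, a journal article condenses the full protocol, and the handling of randomization factors is often left to a statistical analysis plan. That plan exists and is not shown. This stands as a limit: a reader might infer that the trial is committed to an unstratified analysis, and the article does not establish that. But it does not leave the tests open either. It names them, with sidedness and threshold, and defers only subgroups. The point is thus a proposed improvement to the tests as stated.

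A reader might also infer that the trial is underpowered. It is not. The 1078 was calculated for a plain test, and that test keeps about 80% power or more in every scenario above. Stratifying would add a small bonus and would not repair a shortfall. Nor is a positive result in doubt, because the error is in the safe direction.

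Finally, a reader might infer that several tests at 0.05 leave the deciding p value undefined. The section largely answers this: it defines the primary analysis as a comparison of 30-day event rates and assigns proportions to chi-square or Fisher, and the sample size is built on two proportions. The log-rank and Cox analyses follow naturally as additional, so one clarifying sentence is enough.

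**Conclusion.** The point holds as a modest efficiency improvement. The tests stated for the primary composite do not use the factors on which randomization is stratified. If those factors are prognostic, the chi-square test has a true level of about 4.2 to 4.4% under moderate assumed risks and about 3.5% in an extreme case, and about 1 to 3 points of power are forgone. The very strong site variation in the last simulated row takes this to 3.5 points. If stratum and site are not prognostic, the two analyses perform alike.

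The direction follows from the design. The size rests entirely on assumed stratum risks and site variation, since the article reports neither. The Discussion supports a risk gradient with delay but does not quantify it. Planned power and type I error control are not threatened.

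**What to change.** State that the primary 30-day comparison is a CMH test stratified by onset/thrombolysis stratum and site, reported with the stratified risk difference or risk ratio and its 95% CI. This stays with the two-proportion basis of the sample size.

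Set a rule in advance for small sites, for example pooling them by country. The average is only 18 evaluable patients per site in stratum 2, and uneven recruitment would leave some cells much smaller.

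Label the log-rank test and the Cox treatment hazard ratio as supportive and stratify them in the same way. If the statistical analysis plan already says this, confirming it suffices.

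The cost is a few sentences, settled before unblinding. It needs no extra patients or data and no change to the sample size.

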#### Inclusion Criteria

I.Adult patients (≥ 18 years old) presenting with suspected STEMI (new ST-elevation at the J-point in two contiguous leads with the cut-points: ≥ 0.1mV in all leads other than V2-3 where the following cut-points apply: ≥0.2mV in men ≥40 years (≥0.25 mV in men <40 years) or ≥ 0.15mV in women)II.Within 24 h of onset of myocardial infarction as deemed by the attending clinicianIII.Signed informed consent

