### Trial Intervention

An automated pneumatic blood pressure device (manufactured by Seagull Aps in Denmark) will be used to deliver either the RIC or sham protocol. The RIC protocol will comprise of applying the blood pressure cuff at recruitment on the upper arm to automatically deliver four 5-min alternating high-pressure cuff inflations (20 mmHg above each participant’s systolic blood pressure) and cuff deflations, such that the total RIC protocol takes 40 min. The sham control protocol will comprise the application of a visually identical pneumatic cuff on the upper arm which will automatically deliver four 5-min alternating low-pressure cuff inflations (20 mmHg) and cuff deflations, for a total of 40 min. The RIC and sham protocol will be repeated daily over the next two days. Enrolled participants in stratum 1 will receive RIC or sham control within 1 h of thrombolysis. Participants in stratum 2 will receive RIC or sham control within 1 h of randomization. The RIC and sham devices will be applied by the unblinded research nurse. None of the study interventions or procedures will interfere with standard STEMI management at each site. Participants enrolled in the observational arm will not receive any trial intervention.

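### RIC is compared with sham only by unadjusted tests: valid at the planned 80% power, but prespecified adjustment for known baseline values would add precision, by an amount the article does not let us fix

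*Protocol article*

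**What the plan says.** Under Statistical Analysis, the primary analysis compares 30-day event rates between RIC and sham in all randomized patients. Three methods are then named:

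- For proportions: "differences in proportions using the χtest, or Fisher exact test, as appropriate".
- For survival curves: Kaplan-Meier with the log-rank test, with no strata or covariates mentioned.
- For baseline factors: "Cox proportional hazards regression models will be fitted to identify factors associated with the hazard of occurrence of the composite event", reported as hazard ratios with 95% confidence intervals and Wald p values.

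The section refers to a separate statistical analysis plan, but only for the subgroups.

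Elsewhere the article shows which baseline values staff must know:

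- Randomization is stratified by site and time of MI onset (Randomization).
- The ECG criterion, "new ST-elevation at the J-point in two contiguous leads", has cut-points that depend on lead, sex and age (Inclusion Criteria).
- Systolic pressure enters the shock exclusion (Exclusion Criteria) and the cuff setting: the device is to "automatically deliver four 5-min alternating high-pressure cuff inflations (20 mmHg above each" participant's systolic pressure (Trial Intervention).

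**The concern.** Age, sex, systolic pressure and delay from onset plausibly predict death or heart failure after STEMI. The Discussion itself uses ischaemic time, Killip class and comorbidity to separate high-risk from low-risk populations. A crude comparison leaves the outcome variation explained by such factors in the error term. The one regression model named answers a prognostic question and is not said to estimate the effect of RIC.

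What is at stake is efficiency. The design has 80% power at its evaluable size and no margin beyond that. The Introduction attributes the earlier large trial's lack of power partly to an unexpectedly low event rate in its sham group. Precision gained without more patients would be a useful reserve if that happened again.

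**Working it through.** **Inputs from the article.**
- Control risk: "using a primary combined event rate of 30" per cent.
- Effect: "25% relative risk reduction in the 30-day event rate of all-cause death and heart failure hospitalization", so the RIC risk is 0.30 × 0.75 = 0.225 and the difference is 0.075.
- Error rates: "to achieve 80% power, at the 5% significance level"; "All tests will be two-sided".
- Equal allocation; 1078 evaluable (539 per arm); 1200 recruited after 10% drop-out.

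**Assumed input.** R², the share of outcome variance explained by baseline covariates. The article gives no R², C-statistic or risk model, so a range is used.

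**Step 1: reproduce the plan's figure.** The mean risk is (0.30 + 0.225)/2 = 0.2625. With pooled variance under the null:

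n per arm = [1.960·√(2 × 0.2625 × 0.7375) + 0.8416·√(0.30 × 0.70 + 0.225 × 0.775)]² / 0.075²

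= [1.960 × 0.6222 + 0.8416 × 0.6200]² / 0.005625 ≈ 539.1

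This is about 1078 in total, or 1080 if each arm is rounded up. Power at 539 per arm is 80.0%. For drop-out, 1078/0.90 = 1198, consistent with 1200. The plan's figure is therefore sound, and it is the figure for an *unadjusted* comparison.

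**Step 2: power after adjustment.** Adjustment multiplies the variance by about (1 − R²), so the effective size is n/(1 − R²) per arm:

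power = Φ{[0.075·√(n/(1 − R²)) − 1.960 × 0.6222] / 0.6200}

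Example at R² = 0.10: 539/0.90 = 598.9; 0.075 × √598.9 = 1.835; (1.835 − 1.220)/0.620 = 0.993; Φ = 84.0%.

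| Assumed R² | Power, 1078 evaluable | Gain (points) | Power, all 1200 |
|---|---|---|---|
| 0 (crude) | 80.0% | – | 84.0% |
| 0.02 | 80.8% | 0.8 | 84.8% |
| 0.05 | 82.0% | 2.0 | 85.8% |
| 0.10 | 84.0% | 4.0 | 87.6% |
| 0.15 | 86.0% | 6.0 | 89.4% |
| 0.20 | 88.0% | 8.0 | 91.1% |
| 0.25 | 89.9% | 9.9 | 92.7% |

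**Step 3: what these R² values mean.** With a normally distributed risk score on the logit scale and 30% overall risk, R² of 0.07, 0.11, 0.16, 0.20 and 0.25 correspond to C-statistics of about 0.66, 0.70, 0.74, 0.78 and 0.80.

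**Step 4: check by simulation.** Settings: 539 per arm, marginal risks held at 30% and 22.5%, 3000 trials each, crude chi-square against the Wald test of treatment in an adjusted logistic model.

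| SD of log-odds score | Approx. R² | Crude | Adjusted |
|---|---|---|---|
| 0 | 0 | 78.9% | 79.0% |
| 0.6 | 0.07 | 79.7% | 81.7% |
| 0.8 | 0.11 | 81.2% | 85.2% |
| 1.0 | 0.16 | 80.5% | 86.6% |
| 1.2 | 0.20 | 79.1% | 87.1% |
| 1.4 | 0.25 | 80.6% | 90.2% |

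Each figure has a Monte Carlo error of about √(0.8 × 0.2/3000) = 0.7 points. The gains (0, 2, 4, 6, 8 and 10 points) agree with Step 2. With no prognostic information, adjusting for one covariate costs nothing visible.

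**The case against.** **The analysis plan is not shown and may contain an adjusted analysis.** This stands as a limit: nobody can say from the article that no adjusted analysis exists. But the article does name its methods for comparing the arms, and none carries covariates. It cites the analysis plan only for subgroups.

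**The text is looser than a commitment to a crude primary test.** The sentence on proportions is generic, the log-rank test is also named, and the Cox sentence does not exclude treatment arm as a factor. This is fair. The article states unadjusted comparisons and gives the regression a prognostic purpose; it does not rule out an adjusted treatment estimate.

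**A reader might infer that the plan gives up 4 to 8 points of power.** The documents do not support that as a fact. It needs R² of 0.10 to 0.20, and nothing shows that age, sex, systolic pressure and delay reach 0.10. At R² 0.02 to 0.05 the gain is 1 to 2 points.

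**A reader might infer that these values are all in the database already.** The article lists no baseline dataset. Staff must know age, sex, systolic pressure and time from onset, but that does not prove each is stored for analysis. Infarct location is usable only if the ECG leads are captured. Killip class at entry is not said to be collected.

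**A reader might infer that the mix of countries and of thrombolysed and non-thrombolysed patients leaves the crude test open to chance imbalance.** Stratification by site and time of onset largely meets this. Leaving those factors out of the analysis tends to make the crude test slightly conservative, not invalid.

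**Conclusion.** The point holds as an efficiency gain worth taking. The stated comparisons of RIC with sham are unadjusted, and regression on baseline factors is reserved for a prognostic question. The planned tests are valid and reach their stated power; nothing here shows bias or a sample-size error.

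The size of the gain is conditional: roughly 1 to 10 points at 1078 evaluable patients for R² from 0.02 to 0.25, and slightly less from the higher base of 84% if all 1200 are analysed. It rests on the plan's own risks of 30% and 22.5%, on an R² that the documents do not supply, and on a working model that captures most of the covariates' prognostic value. The simulation used a correctly specified model with a continuous score. Binary covariates, or a systolic range narrowed by the shock exclusion, would put the trial nearer the lower end.

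**What to change.** Before unblinding, prespecify one primary treatment-effect model for the 30-day composite, for example logistic regression followed by standardisation over the trial population. Include:

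- treatment arm;
- the stratification factors (site, with a rule for pooling small sites, and the time-of-onset stratum);
- a short fixed list of values measured before randomization: age, sex, systolic pressure, hours from onset, and infarct location if it is captured from the ECG.

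Report the marginal risk difference and relative risk with 95% CI. Keep the crude test as supportive and label the prognostic Cox model exploratory. Quote any expected gain in power as conditional on R².

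The cost is a paragraph in the analysis plan and a few lines of code. It needs no more patients, and no new measurements provided the listed values are stored. The small downside is that the covariates, their functional form and a simple rule for missing baseline values must be fixed in advance, so that they cannot be chosen after results are seen. If the unseen analysis plan already does this, the article's wording only needs to be brought into line.
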